### Randomization and Blinding

Participants will be randomized in a 1:1 ratio to either the control group (CG) or the IG. The randomization sequence will be generated using an online randomizer (Sealed Envelope; Sealed Envelope Ltd) by an investigator who is not involved in patient recruitment, assessment, or intervention and who will perform the group allocation. Group allocation will be concealed using consecutively numbered, sealed, opaque envelopes. Randomization will be stratified by diagnosis (ILD or COPD).

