### Statistical Analysis

The sample size calculation, based on the primary outcome of the study (EQ-5D-5L), was informed by a previous study reporting an observed difference of 0.04 in the EQ-5D-5L index, which was considered clinically meaningful within that specific study population [13]. This value was used as a pragmatic estimate of the expected effect size for sample size determination. The calculation was performed using G*Power software (*F* tests: ANOVA, repeated measures, within-between interaction). The calculation assumed an effect size of *f*=0.25, a 2-sided α level of .05, and a statistical power of 90% (β=.10). The design included 2 groups and 4 repeated measurements, with a correlation among repeated measures of 0.5 and a nonsphericity correction (ε) of 0.5. On the basis of these assumptions, the required sample size was 50 participants (25 per group), with an achieved power of 0.91. Considering an anticipated dropout rate of 20%, the final target sample size was increased to 30 participants per group to preserve statistical power under an intention-to-treat framework. The significance level will be set at 5% (*P*<.05) for all statistical tests, which will be conducted using GraphPad Prism (version 5.0; GraphPad Software LLC).

Data normality will be assessed using the Kolmogorov-Smirnov test, and homoscedasticity will be evaluated using the Levene test. Parametric data, defined by a normal distribution as demonstrated by histograms, will be presented as means and SDs (or SEs), while nonparametric variables will be presented as medians and IQRs.

Longitudinal outcomes will be analyzed using linear mixed-effects models with fixed effects for group, time, and group-by-time interaction and random intercepts for participants. The results will be interpreted in light of the established MCIDs for each outcome measure. Additionally, as a complementary analysis, the proportion of participants in each group achieving a within-individual change equal to or greater than the MCID will be calculated, providing a more clinically meaningful interpretation of the findings. Sensitivity analyses will be conducted to assess the robustness of the results.

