The adherence criterion will be used in exploratory subgroup analyses to compare outcomes between adherent and nonadherent participants [25]. All primary longitudinal analyses will follow a modified intention-to-treat approach, including randomized participants who initiated follow-up and contributed data to the longitudinal analysis, regardless of adherence status. This approach preserves the benefits of randomization and reflects real-world conditions. Sensitivity analyses will be conducted to assess the robustness of the results.

For exploratory purposes, when appropriate, comparisons between groups at specific time points may be performed using parametric or nonparametric tests (eg, the *t* test or Mann-Whitney test), depending on data distribution. Pearson correlation coefficients will be used to assess associations between normally distributed variables, while Spearman correlation coefficients will be used for nonnormally distributed variables.

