## Results

Funding and ethics approval were obtained in April 2023. Recruitment began in January 2024 and was completed in May 2026. A total of 62 participants were randomized, of whom 60 initiated follow-up and were included in the longitudinal analysis. Overall, 49 participants completed the 90-day follow-up. Data collection has been completed, and data analysis is ongoing. The results are expected to be submitted for publication in the first half of 2027.

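### Optional single-visit comparisons by a t test or Mann-Whitney test chosen from the data give up what the planned mixed model already provides (minor)

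*Protocol article*

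**What the plan says.** In the protocol article (Methods, Statistical Analysis), longitudinal outcomes are analysed by a linear mixed model with group, time, their interaction and a random intercept per participant. Results are to be read against each outcome's MCID. The modified intention-to-treat rule covers the primary longitudinal analyses.

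The section ends with an exploratory, conditional allowance: "comparisons between groups at specific time points may be performed using parametric or nonparametric tests". The t test and the Mann-Whitney test are given as examples, and the distribution of the data decides between them. No visits are named.

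Two statements concern distribution. One reads "Data normality will be assessed using the Kolmogorov-Smirnov test". The other, beginning "Parametric data, defined by a normal distribution as demonstrated by histograms", governs whether a variable is summarised by mean and SD or by median and IQR. The 5% level applies to every test.

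The Results section reports 62 randomised and 60 who started follow-up. It adds: "Overall, 49 participants completed the 90-day follow-up". It gives no split by arm and no reasons for loss.

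**The concern.** A two-sample test at one visit uses only those with a value at that visit. The article does not use the term available cases, but these tests work that way and no imputation is named for them. The mixed model also uses the earlier scores of people who later leave, which protects it when dropout depends on observed scores.

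Differential dropout is plausible here. The Interventions section gives the intervention arm calls every 15 days against every 30 in the control arm. Calls are used to encourage questionnaire completion, and the intervention arm may receive extra contact after alerts. The Discussion accepts that the unequal contact may affect adherence and perceived health.

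The two tests also answer different questions. The t test compares means; the Mann-Whitney test compares the ordering of the two distributions. If the data choose the test at each visit, one outcome can be tested for different things at days 30, 60 and 90. A Mann-Whitney P value gives no difference in scale points to set against an MCID.

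At stake is a day-90 exploratory result that disagrees with the model's own day-90 estimate for reasons unrelated to the intervention.

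**Working it through.** **1. The plan's own figure.** The inputs from Statistical Analysis are f = 0.25, α = 0.05 and "2 groups and 4 repeated measurements, with a correlation among repeated measures of 0.5 and a nonsphericity correction (ε) of 0.5". For the within-between interaction with N = 50, k = 2 groups and m = 4 measurements:

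- λ = f²·N·m·ε/(1 − ρ) = 0.0625 × 50 × 4 × 0.5/0.5 = 12.5
- df1 = (k − 1)(m − 1)ε = 1.5
- df2 = (N − k)(m − 1)ε = 48 × 3 × 0.5 = 72

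The noncentral F power is 0.909. The article says "the required sample size was 50 participants (25 per group), with an achieved power of 0.91", so the figure reproduces. The single-visit tests do not enter it, and nothing below changes it.

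**2. How many lack day 90.** 60 − 49 = 11, or 11/60 = 18.3%, taking completers as those with day-90 values.

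**3. Bias from dropout (assumed data).** Four visits were simulated with correlation 0.5 (the plan's value), SD 1 and no true effect. Dropout at each visit followed logit P = −2.75 + s × previous score, with the slope s set separately by arm. One very large sample (400,000) was used so that bias is visible. The model contrast is the day-90 difference from a saturated group-by-time fit.

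| s, control / intervention | Retained at day 90, control / intervention | Observed-value difference (SD) | Model contrast (SD) |
|---|---|---|---|
| 0 / 0 | 83.1% / 83.2% | −0.004 | −0.004 |
| −1 / −1 | 77.3% / 77.4% | −0.003 | −0.003 |
| −1 / 0 | 77.3% / 83.2% | −0.113 | −0.004 |
| −1 / +1 | 77.3% / 77.2% | −0.223 | −0.004 |

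A separate simulation at trial size (30 per arm, about 49 with day-90 data, 2,000 trials per scenario) agrees. With arm-dependent dropout, the day-90 t test had bias of 0.15 to 0.18 SD and type I error of 8% to 9%. The model contrast had bias of at most 0.02 SD and error of 4.7% to 5.4%. Under random dropout both were valid, with SEs of 0.285 SD (t test) and 0.278 SD (model), a ratio of 1.025.

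The article gives no SD for the EQ-5D-5L index, so these biases cannot be put in index points. A bias of 0.223 SD would equal the planning difference of 0.04 if the SD were 0.04/0.223 = 0.18. A bias of 0.113 SD would do so if the SD were 0.04/0.113 = 0.35.

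**4. Change of test between visits (assumed data).** Suppose each arm is screened at 5% at each of three visits and either rejection triggers the rank test. Let q be the chance of a switch to the rank test at one visit. If visits were independent, P(tests differ across visits) = 1 − (1 − q)³ − q³.

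- Normal data, corrected Kolmogorov-Smirnov: q = 1 − 0.95² = 0.0975, which gives 1 − 0.735 − 0.001 = 0.26. Simulated with correlated visits: 25%.
- Skewed data, corrected: simulated q = 0.687, which gives 1 − 0.324 − 0.031 = 0.65. Simulated: 64%; the separate simulation gave 63% to 68% for skewness of −0.8 to −1.4.
- Mild ceiling, corrected: simulated 27%.
- Uncorrected Kolmogorov-Smirnov: under 2% rejection per arm, so q < 1 − 0.98² = 0.040 and P < 1 − 0.886 = 0.11. The screen then does almost nothing.

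**5. What the model already gives.** The day-90 difference is the group coefficient plus the group-by-day-90 coefficient, in scale points and with a CI. Days 30 and 60 follow in the same way.

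**The case against.** The strongest answer is the standing of the sentence. The tests are exploratory, conditional, permissive and named only as examples. The mixed model is the stated analysis, and nothing bars reporting visit contrasts from it. All of that stands and limits the point to a minor one.

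Four stronger readings are tempting, and the article does not support them:

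- A reader might infer that the primary comparison rests on these tests or is biased by them. It does not; the mixed model is untouched.
- A reader might infer that the day-90 t test is biased. With no true effect, bias appeared only when score-related dropout differed by arm. Score-related dropout of the same form in both arms gave about zero. The article reports neither dropout by arm nor reasons.
- A reader might infer two rival rules for choosing the test, Kolmogorov-Smirnov and histograms. The histogram sentence governs how data are presented, not which test is used. Finer detail of the screen may lie in an analysis plan that is not shown.
- A reader might infer that every rank test should go. A rank test is a reasonable check on a 0-4 ordinal scale such as the mMRC.

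The simulations also rest on assumed mechanisms, and the model comparison used the true covariance, which favours the model. The switching rate runs from below 11% to 68% depending on the form of the test and the skewness. What survives is that the choice of test is driven by the data, the tests discard earlier visits, and the planned model supplies a better estimate at no extra cost.

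**Conclusion.** The point holds as a minor one about an optional analysis. A single-visit t test or Mann-Whitney test loses the information in earlier visits that the planned model uses for the roughly 11 of 60 without day-90 completion. If score-related dropout differs by arm, the illustrative bias is 0.11 to 0.22 SD, against at most 0.02 SD for the model. If it does not differ, the bias is about zero, and under random dropout the gain is only a 2.5% difference in SE. The protection assumes that dropout depends on observed scores and that the model's covariance is about right.

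The possible change of hypothesis between visits, and the lack of a scale-point difference from the Mann-Whitney test, need no dropout assumption. The stated sample size and power do not change.

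**What to change.** Replace the exploratory sentence with wording to this effect: between-group differences at days 30, 60 and 90 will be estimated, with 95% CIs, as contrasts from the longitudinal mixed model. Check the model's residuals instead of using a normality screen on raw data to select a test. If a rank test is kept, for example for the mMRC, fix it in advance for that outcome at all visits and label it a supportive check. Because the Results section says that data collection is complete and analysis is under way, date the change.

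The cost is wording only: no new data, no new model and no change to the sample size. The small downside is that the contrasts depend on the model's covariance and residual assumptions, including the random-intercept structure.

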### Ethical Considerations

The study has already been approved by the Hospital das Clínicas, University of São Paulo Medical School research ethics committee (6.012.012) and registered at ClinicalTrials.gov (NCT06882265). Any important protocol modifications will be submitted to the research ethics committee and updated on ClinicalTrials.gov. All participants will receive verbal and written information about the study and will provide signed informed consent before participating. Information collected from participants is accessible only to the research team and is individually identifiable by a unique numeric ID code. All electronic data are stored using this code, ensuring that no identifiable information is retained until study completion. Confidential information is stored in locked filing cabinets, and only deidentified data will be presented or published. A formal data monitoring committee was not considered necessary due to the low-risk nature of the intervention and the short follow-up period. Trial conduct and data quality will be monitored by the research team throughout the study.

## Results

Funding and ethics approval were obtained in April 2023. Recruitment began in January 2024 and was completed in May 2026. A total of 62 participants were randomized, of whom 60 initiated follow-up and were included in the longitudinal analysis. Overall, 49 participants completed the 90-day follow-up. Data collection has been completed, and data analysis is ongoing. The results are expected to be submitted for publication in the first half of 2027.

## Discussion

Individuals receiving LTOT represent a particularly vulnerable subgroup of patients with chronic respiratory diseases. They often experience severe functional limitations, reduced autonomy, and high rates of health care use, making them an ideal target population for interventions aimed at improving self-management and HRQoL [26]. ILD and COPD account for most LTOT prescriptions and are associated with a high symptom burden and progressive clinical decline [27].

Moreover, among patients with chronic respiratory diseases, especially those with COPD and ILD, heterogeneity in beliefs and perceptions about the disease can significantly influence symptoms, quality of life, and self-management capacity. In addition, frequent remote monitoring may negatively affect emotional well-being in some individuals by increasing health-related anxiety or symptom awareness. Therefore, assessing anxiety and depression symptoms using the HADS may provide important information regarding the psychological impact of remote monitoring in this population. An analysis conducted among patients with COPD identified 2 distinct profiles: a “distressed” group characterized by a higher emotional burden, worse HRQoL, increased dyspnea, and lower self-efficacy; and a “coping” group with more adaptive perceptions. Despite similar levels of lung function and physical activity, these profiles showed relevant clinical and psychosocial differences, highlighting the importance of routinely assessing disease perceptions to personalize interventions and optimize clinical outcomes [28]. In this context, remote monitoring appears to be a suitable method for following patients receiving LTOT, as it enables continuous tracking of parameters such as oxygen saturation, respiratory rate, and physical activity, facilitating the early detection of clinical decompensation. These technologies encourage self-care by increasing patients’ awareness of their condition, which is essential for improving treatment adherence and quality of life [29,30]. However, longer follow-up periods may be necessary to detect more consistent and clinically meaningful changes in HRQoL. Despite these potential benefits, remote monitoring faces significant challenges. The heterogeneity of available devices and the need for adequate technological infrastructure are barriers to the widespread adoption of this technology [10]. Additionally, adherence to LTOT and patients’ perceptions of oxygen therapy may vary and may influence the effectiveness of home-based monitoring [31,32].

If the study findings confirm our hypothesis, they will align with previous research indicating that digital health interventions can enhance patient engagement and emotional well-being by providing a sense of connection and safety within the home environment. Few studies have evaluated the clinical outcomes of remote monitoring specifically in patients receiving LTOT, highlighting the need for further research in this population. Therefore, this study seeks to provide evidence to support the safe implementation of home care services, and the results are expected to guide clinical practice and future home care strategies.

This study has some anticipated limitations. The sample size may not have adequate statistical power for the secondary outcomes. Although the follow-up period may be considered short, it should be sufficient to detect changes in quality of life and assess participants’ adherence. The frequency of data collection differed between groups, reflecting the distinct nature of the approaches: the CG performed self-monitoring, whereas the IG received more intensive remote monitoring. However, this difference may influence outcomes such as adherence and health perception. On the other hand, this design makes the comparison more conservative and closer to real-world clinical practice, allowing an evaluation of the incremental value of remote monitoring over standard care.

The potential clinical implications of this research include validating remote monitoring as an effective tool for optimizing the management of home oxygen therapy. This approach may enable faster and more personalized interventions, promote greater patient autonomy, and improve quality of life, thereby contributing to better health outcomes.

## Data Availability

The datasets used and/or analyzed during the study are available from the corresponding author upon reasonable request.

## Appendix

Multimedia Appendix 1 SPIRIT checklist.

## Abbreviations

CAT: COPD Assessment Test
CG: control group
COPD: chronic obstructive pulmonary disease
HADS: Hospital Anxiety and Depression Scale
HADS-A: Hospital Anxiety and Depression Scale–anxiety
HADS-D: Hospital Anxiety and Depression Scale–depression
HR: heart rate
HRQoL: health-related quality of life
IG: intervention group
ILD: interstitial lung disease
K-BILD: King Brief Interstitial Lung Disease
LTOT: long-term oxygen therapy
MCID: minimal clinically important difference
mMRC: modified Medical Research Council
SPIRIT: Standard Protocol Items: Recommendations for Interventional Trials
SpO2: peripheral oxygen saturation
VAS: visual analog scale
